### Study objectives (rationale and comparators)

This experimental study aims to investigate whether worry and rumination, two forms of RNT, share underlying cognitive mechanisms. We focus on negative interpretation bias, a transdiagnostic cognitive process prevalent in GAD and depression (see ref. 14) and shown to play a causal role in influencing levels of worry^17^ and rumination^19^ in single-session experimental studies. Using CBM-I, we investigate whether repeatedly training positive interpretations over multiple sessions (vs an active control condition) leads to a sustained reduction in worry and rumination in the disorders in which they play central maintaining roles, namely GAD and depression. Individuals with GAD or depression will receive worry-related or rumination-related training materials, respectively, to maximise potential training of interpretations relevant to the key form of RNT for the given disorder. We assess interpretation bias, levels of worry and rumination (primary outcomes) as well as anxiety and depression symptoms (secondary outcomes) at baseline (study visit 1) and again after multisession CBM-I or active control sessions (study visit 2). In addition, we examine the sustained impact of training positive interpretations on levels of worry, rumination, anxiety and depression at 1-month follow-up. Further, we compare two types of CBM-I, with and without prior RNT, to examine whether activating RNT modulates the effects of CBM-I in individuals with GAD and depression. Finally, to consider how cognitive processes may influence each other, and drawing on the combined cognitive bias hypothesis^36^ as well as building on findings that single-session CBM-I increases attentional control during worry,^18^ we include a classic Stroop and emotional Stroop task to examine whether multisession CBM-I impacts the ability to inhibit irrelevant and RNT-related information.

### Hypotheses

For both diagnostic groups, we predict that CBM-I with and without prior RNT will reduce negative interpretation bias, RNT (levels of worry and rumination) and psychological distress (levels of anxiety and depression) relative to the active control condition. Furthermore, we examine whether an induced period of RNT prior to CBM-I either enhances the effects of training (by activating underlying cognitive biases, as in attention bias research), or reduces training effects (potentially due to the additional demands placed on attentional control resources by RNT). Finally, and crucially given its proposed underlying role, we expect that effects of CBM-I on worry and rumination, anxiety and depression will be driven by changes in interpretation bias.

## Methods

### Design

Individuals meeting Diagnostic and Statistical Manual of Mental Disorders Fifth Edition (DSM-V) diagnostic criteria for either GAD or current major depressive episode (MDD) will be randomly allocated to one of three conditions: CBM-I with prior RNT (henceforth CBM_RNT), standard CBM-I without prior RNT (henceforth CBM_STAND) or an active control condition (henceforth CONTROL). To investigate the impact of CBM-I on changing interpretation bias, near transfer will be assessed using measures of interpretation bias. To explore the impact of CBM-I on measures of RNT and psychological distress, far transfer will be assessed by changes to levels of worry and rumination (assessed using a behavioural task and self-report questionnaires) as well as self-report measures of anxiety and depression symptoms following 10 internet-based CBM-I or active control sessions over the course of 3 weeks. Impact on all questionnaire measures will additionally be assessed at 1-month follow-up.

### Participants and recruitment

Participants with GAD or MDD will be recruited from the community in Greater London via online advertisements and university circular emails. Participants must be able to attend two experimental sessions at the Institute of Psychiatry, Psychology and Neuroscience, King's College London, located in South London (see figure 1 for the study flow chart). Participants will be fluent English speakers aged between 18 and 65 years old. They will be screened for levels of anxiety and/or depression, and participants with a total score <10 or five items scored <2 including items 1 and/or 2 on Patient Health Questionnaire 9 (PHQ-9)^37^ and/or with a total score <10 or item 2 scored <2 on GAD-7^38^ will be excluded. Further exclusion criteria are severe depression (>23 PHQ-9 total score), past or current risk to self (self-harm in past 12 months/suicide attempt in last 5 years/PHQ-9 suicidal ideation item 9 scored >1^39^), comorbid psychosis, bipolar disorder, borderline personality disorder or substance abuse, non-normal/not corrected to normal hearing (as the study involves listening to audio clips) as well as current or recent (past 6 months) psychological treatment. Further, individuals taking psychotropic medication must have been stabilised on that medication for at least 3 months without remission to be included. The latter two criteria serve to ensure that any positive effects of CBM-I are not confounded by ongoing improvements due to other treatments. Diagnosis of GAD or MDD will be confirmed using the Structured Clinical Interview for DSM-V axis I disorders (SCID^40^) at an initial assessment prior to the first experimental session. Authors CK and JW will administer the diagnostic interviews. A clinician will blind-code a subset of interviews to assess reliability. Participants meeting diagnostic criteria for both GAD and MDD, that is, participants with current comorbid GAD and MDD, will be excluded.

**Figure 1 BMJOPEN2016013404F1:**
[figure not shown]
Study flow chart.

#### Sample size

Prior single-session CBM-I research with participants with GAD has indicated that CBM-I training (vs control) had a large effect on the breathing focus thinking task (*f^2^*=0.43,^17^ see below for task description). Using G*POWER software^41^ to calculate sample sizes achieving 80% power at p=0.05, N=49 in each group (16 per condition) would be needed to reveal a large effect size on the breathing focus task. We based our power calculation on this far transfer task because far-transfer is more difficult to achieve than near transfer, and near-transfer effects of multisession CBM-I training have been found to be large (see ref. 42). Based on this calculation, we aim for a final cell size of at least n=20 participants per condition in each diagnostic group.

#### Randomisation and blinding

Participants will be randomised to one of the three conditions on the basis of a random allocation sequence generated on http://www.random.org by a person not involved in the research study. As in Williams, Blackwell, Holmes and Andrews,^39^ numbers 1–3 corresponding to the three conditions will be placed in sealed envelopes, the envelopes marked with the ascending sequence order number, and participants allocated to conditions according to this sequence. Participants will remain blind to the condition until the end of the study (when they will be debriefed). Researchers will open the envelope at the first experimental session once participants have provided written informed consent. Blinding of the researchers will not be possible as researchers guide participants through the first online session, which differs by experimental condition (see below).

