### Primary outcome measures

#### Interpretation bias (near transfer)

*Scrambled sentences test* (based on ref. 51): The scrambled sentences test involves reordering a list of words to form sentences. Participants use five of six presented words to form grammatically correct sentences, which can either be of negative or positive valence. For example, ‘looks the future bright very dismal’ may be unscrambled to form the sentence ‘the future looks very bright’ (positive) or ‘the future looks very dismal’ (negative). Participants are told to form the first sentence that comes to mind (rather than select a particular valence). In the present study, participants unscramble 20 sentences in 5 min, while holding in mind a string of six digits, as such a cognitive load depletes cognitive resources and is thus thought to present a truer reflection of participants' interpretative style.^51^ Half the sentences are related to worry themes (see themes above) and were generated by the authors, while half are related to depressive rumination and were selected from Wenzlaff and Bates^51^ and Wenzlaff and Bates.^52^ The number of negative sentences divided by the total number of grammatically correct sentences generated serves as an index of interpretation bias, with a higher index (scores range from 0 to 1) denoting a more negative interpretation bias. The test can be scored across all items or for worry and depressive rumination items separately. The scrambled sentences test is administered at the first and second study visit; thus, two separate lists of 20 items were created and the order is counterbalanced across participants.

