## The day trip

Friends of yours have organised a day trip. You have been feeling quite low and wonder whether to join them. In the end, you decide to go along. Afterwards, you think back over the day and how going along made you (f e – l) [feel].Did you go on a day trip with your family? (Yes/No)
You felt better after going on the day trip (positive target)Going on the day trip made you feel worse (negative target)The car journey went very smoothly (positive foil)The car broke down on the way home (negative foil)Participants complete the recognition memory test at the beginning and end of the first study visit (before and after the first online session) and at the second study visit; hence, three separate lists of 20 items were generated and the order is counterbalanced across participants.

### 

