**Figure 2 BMJOPEN2016013404F2:**

Participant flow chart with measurement points.

At the first study visit (experimental session), participants provide written informed consent and will be randomised by diagnostic group to one of the three conditions: (1) CBM_RNT, (2) CBM_STAND or (3) CONTROL (see the Experimental conditions section above for details). They will then complete the scrambled sentences test, classic and emotional Stroop task, recognition memory test and breathing focus task. Then, participants will be given the study rationale for the online homework sessions and will complete expectancy and acceptability ratings before completing the first online session on the study website. This is completed during the study visit to ensure participants understand the instructions for their condition and are able to complete the sessions correctly. Each session includes the RNT induction (CBM_RNT) or neutral task (CBM_STAND and CONTROL conditions), followed by 50 scenario audio clips (see above) with a short break after 25 scenarios. In addition, participants complete ratings of state levels of worry, rumination, anxiety and depression after the prescenario task (RNT or neutral task) and at the end of each session. Following the first online session, participants complete the recognition memory test again (different scenarios; see above) to assess change from pre to post first study visit. Finally, participants are presented with instructions for completing the nine online sessions over the course of the next 3 weeks, and the researcher will complete a diary card with each participant to help schedule the homework sessions.

Participants will complete three online sessions per week over the next 3 weeks, with some flexibility in terms of dates and times of day, and with the provisos that they complete no more than one homework session per day and complete the homework sessions within 1 month and the final session no later than the day before their second study visit. Researchers will monitor adherence to the homework sessions using the online platform. They will keep in touch with participants by using participants' preferred method of contact (email, phone, SMS) to facilitate engagement and trouble shoot issues with the online sessions, and will encourage participants to catch up missed sessions. Participants are required to complete a minimum of eight sessions (see also the Statistical methods section).

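### The allocation envelope is opened before the visit 1 baseline tasks, although the stated reason for unblinded researchers applies only from the first online session

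*Protocol article*

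**What the plan says.** Under Randomisation and blinding, the protocol article states: "Researchers will open the envelope at the first experimental session once participants have provided written informed consent". It continues: "Blinding of the researchers will not be possible as researchers guide participants through the first online session, which differs by experimental condition". Participants stay blind until they are debriefed.

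The Procedure section (text after Figure 2) gives the same order for visit 1. First, "participants provide written informed consent and will be randomised by diagnostic group to one of the three conditions". Next, "They will then complete the scrambled sentences test, classic and emotional Stroop task, recognition memory test and breathing focus task". After that, participants are given the rationale for the homework sessions and "will complete expectancy and acceptability ratings before completing the first online session on the study website".

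The section on primary outcome measures lists the scrambled sentences test, the recognition memory test, the breathing focus task and three questionnaires (PSWQ, RRS, RNTQ). The Stroop tasks, PHQ-9 and GAD-7 are secondary. On timing, the article says: "The scrambled sentences test is administered at the first and second study visit". The recognition memory test is given before and after the first online session and again at visit 2. All five questionnaires are completed online in the 24 hours before visit 1.

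**The concern.** The reason offered for not blinding researchers is sound for the first online session, because its content differs by condition. It does not cover the tasks that come earlier in the same visit. Nothing in the description of the four baseline tasks differs by experimental condition; the breathing focus task varies only by diagnostic group (worry or rumination). The design therefore gives up blinding of the task baselines without a stated need.

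The analysis models use condition and time point as predictors (Statistical methods), so visit 1 is the reference for change on every task measure. If a researcher who knows the allocation instructs, paces or encourages participants differently by condition, the difference enters that reference. An imbalance between conditions at baseline could then no longer be put down to chance alone. The rationale and the expectancy ratings are exposed in the same way, and they are a natural point for a researcher's expectations to reach the participant.

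**Working it through.** The plan gives no figure to reproduce. The main check compares the order of events with the reason given for not blinding.

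**Order at visit 1 (Randomisation and blinding; Procedure)**

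1. Written consent.
2. Envelope opened, allocation known to the researcher.
3. Baseline scrambled sentences, classic and emotional Stroop, recognition memory, breathing focus.
4. Study rationale, then expectancy and acceptability ratings.
5. First online session, the first step described as differing by condition.

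The stated reason for unblinding starts at step 5. Steps 3 and 4 fall between unblinding and that reason. The two sections agree with each other, so this is the intended design and not a contradiction.

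**Which baselines are exposed**

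- Scrambled sentences (primary): after the envelope. The participant completes it within a fixed 5 minutes.
- Recognition memory (primary): after the envelope. The participant gives the ratings.
- Breathing focus (primary, and the basis of the sample size): after the envelope. It has fixed periods and randomly cued sampling, and the audio is later coded by an assessor blind to condition.
- Classic and emotional Stroop (secondary): after the envelope. Participants read aloud to the experimenter, with time as the outcome.
- PSWQ, RRS, RNTQ (primary), PHQ-9, GAD-7 (secondary): before the visit, hence before the envelope. Not exposed.

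Three of the six instruments listed as primary are exposed. Only the Stroop is explicitly performed to the experimenter.

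**Illustration of size (assumed inputs)**

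The cell size of 20 per condition is from the Sample size section. The pre-post correlation r = 0.5 and the shifts below are assumptions; the article gives neither.

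The standard error of a difference in change between two conditions, in SD units, is √(2(1 − r)) × √(2/n) = √1 × √(2/20) = 0.316.

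If a bias of b1 at visit 1 and b2 at visit 2 separates two conditions, the bias in the change is b2 − b1. With a net shift δ, the two-sided 5% test rejects a true null with probability Φ(−1.96 + δ/SE) + Φ(−1.96 − δ/SE):

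- δ = 0.1: δ/SE = 0.316, giving about 0.06.
- δ = 0.2: δ/SE = 0.632, giving 0.097.
- δ = 0.3: δ/SE = 0.949, giving 0.158.
- b1 = b2: δ = 0, giving 0.05.

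If the baseline were a covariate instead, a 0.2 SD baseline shift would carry over as r × 0.2 = 0.1. The SE would be √(1 − 0.25) × 0.316 = 0.274, so δ/SE = 0.365 and the result is about 0.065.

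The answer runs from no inflation to about 16%, depending entirely on values that the document does not supply.

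**Reach of a change now**

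The planned total is 2 × 60 = 120, and 59 participants had completed the study at submission. At most 120 − 59 = 61 could still be enrolled under a new order, and fewer if some of these had already attended visit 1.

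**The case against.** A reader might infer that the baseline of every primary outcome is compromised, or that type I error is raised to 10% or more. The document supports neither. The self-report baselines precede allocation. Participants are blind, the scrambled sentences and recognition tests rest on the participants' own responses, and the breathing focus audio is coded blind. The shifts behind the error rates are assumed. That the person who opens the envelope also runs the tasks is itself an inference, although no separate blind tester is described.

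A reader might also say that early opening biases the comparison through participants who stop during the task battery. It does not affect the planned estimate: the analysis takes only those who complete at least 8 of 10 sessions and return for visit 2, so such participants are excluded under either order.

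The strongest counterargument concerns visit 2. Researchers are unblinded there too, and a habit that is the same at both visits cancels in the change score. Blinding the baseline alone would remove that cancellation. This is correct arithmetically, and it limits what the change can be said to achieve. It does not justify the present order, because nothing in the plan makes the two influences equal, and a baseline taken before allocation is known needs no such assumption.

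Two practical points also stand. The article does not say that the rationale is the same in all conditions; if it is not, the researcher needs the allocation before giving it. Assigning another researcher to visit 2 would not by itself secure blinding, because researchers also monitor homework and troubleshoot sessions.

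None of this supplies a reason for opening the envelope before the baseline tasks.

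**Conclusion.** The concern holds in a limited form. The envelope is opened before the baseline of three task-based primary outcomes and the Stroop tasks, and the stated reason for unblinded researchers does not extend to that part of the visit. The exposure is clearest for the Stroop. For the three primary tasks it works through instruction and interaction, and blind participants and, for breathing focus, blind coding reduce it. The questionnaire outcomes are unaffected.

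The size of any bias cannot be derived from the document, and the error rates shown are illustrative only. The conclusion about ordering does not depend on them. It rests on the stated sequence and on the inference that researchers who know the allocation are present for the baseline tasks. Severity is moderate to minor: this is an almost free improvement, and it does not invalidate the trial.

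**What to change.** Amend Randomisation and blinding and the Procedure section so that the envelope is opened only after the baseline breathing focus task is finished. If the rationale is the same in all conditions, open it later still, after the rationale and the expectancy ratings and immediately before the first online session. If the rationale differs by condition, say so, and open the envelope between the breathing focus task and the rationale.

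Apply the new order to participants who have not yet attended visit 1, and report how many were enrolled under each order. State that the change blinds the task baselines only, and list unblinded researchers at visit 2 as a limitation.

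The visit, staff, tasks and allocation sequence stay as they are. The cost is a short amendment and two baseline procedures within one trial, which is why the numbers under each order need reporting.

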### Experimental conditions

All three experimental conditions comprise 10 sessions: 1 initial session at the first study visit and 9 sessions to be completed at home using a purpose-built online platform over the course of 3 weeks (participants are instructed to aim to complete 3 sessions per week). All online sessions begin with the prescenario RNT induction (CBM_RNT) or neutral task (CBM_STAND or CONTROL). Subsequently, participants listen to 50 audio clips (henceforth scenarios) per session and answer a corresponding question after listening to each scenario. All scenarios were audio-recorded by a professional actress and are presented to participants via headphones. In keeping with CBM-I research (see ref. 16), instructions in all conditions emphasise that participants should imagine themselves in the situations the scenarios describe and try to anticipate the ending of each scenario. Mood ratings are obtained after the RNT induction or neutral task and at the end of each session (see also below).

#### Prescenario task: RNT induction and neutral task

*RNT induction**:* The RNT induction consists of a 5-min task, adapted from Hertel, Mor, Ferrari, Hunt and Agrawal,^19^ which is completed as part of each online session prior to the CBM-I scenarios in the CBM_RNT condition. Participants first select a theme about which they have found themselves worrying (GAD group) or ruminating (MDD group) on the day of the session or very recently. Participants have the choice of three common themes (performance, social relationships, or illness and harm for GAD worry; abilities, social relationships, or feeling low for depressive rumination) which correspond to the main themes reflected in the CBM-I and control scenarios (see below). Each theme may be selected once a week (three times in total) to ensure that all participants engage in RNT about themes relevant to the training/control materials. Following the selection of the theme, participants rate the frequency with which they have recently (past few days) thought about a topic relating to this theme and how distressing this has been for them. Then, participants are asked to write a one-line summary of their worry/ruminative thoughts on their selected topic, which is fed back to them on a subsequent screen. Participants are next prompted to identify negative thoughts relating to their topic. To facilitate this, participants with GAD see the prompts ‘When you worry about [one-line summary of topic], what do you fear might happen?’, while participants with depression see the prompt ‘When you ruminate about [one-line summary of topic], what negative thoughts do you have?’ Following this, participants are instructed to write down their stream of thoughts for 3 min:Now, still focusing on **[****one-line summary of topic****]**, please write down the negative thoughts you usually have when you **worry/ruminate**^[i]^ about this.Please don't be concerned about grammar or your thoughts jumping around, but rather try and **write down your thoughts about this topic as they naturally occur**. You don't need to provide any background information; just start with the first thought that comes to mind.We ask you to try and write for the full **three minutes**. After three minutes, the screen will change automatically.Please begin now.

This 3-min period of writing is intended to help participants activate themes of worry/rumination on the designated topic and is followed by a 2-min period of silent worry/rumination in participants' usual manner (akin to refs. 43 and 44):Now please continue to think as you usually would about [**one-line summary of topic**] for two minutes.You can close your eyes to do this, and a beep will sound at the end of the two minutes.If you notice your mind wandering to thoughts that are not distressing or worrying/ruminative, please try to bring your mind back to worrying/ruminating about [**one-line summary of topic**].Please press ‘next’ to begin.

Following this, participants complete ratings of their current level of worry, rumination, anxiety and depression, which serve as manipulation checks (see below).

*Neutral task**:* To minimise the opportunity for spontaneous RNT and to control for the time that participants are engaged in the RNT task, participants in the CBM_STAND and CONTROL conditions complete a neutral task. This 5-min task consists of reading a short story, divided into eight sections, and making a grammatical correctness judgement about the last sentence of each section. At the end of the eight sections, participants complete a comprehension question about the story content, designed to enhance engagement with the task. The presentation of each section is timed to ensure that the duration of the task is matched to the RNT induction. Participants read a different story at each session (order randomised across participants). Subsequently, participants complete the same ratings of current worry, rumination, anxiety and depression as participants in the CBM_RNT condition. A subset (five) of stories was initially piloted in N=23 participants (unrelated to the current study) and stories were judged to be emotionally neutral (mean valence rating on a 100-point visual analogue scale with anchors *very negative/very positive* =59, SD=1.41).

